### Intervention

In study centres of the intervention arm, the POC-CCA-TBST is being implemented among pregnant women between week 20 of pregnancy and delivery and at 9 months after delivery and among their babies at 9 months of age. The urine-based POC-CCA-test is done, and PZQ treatment is offered in case of a positive diagnosis. In the study centres of the control arm, no TBST is carried out, and in case of clinical suspicion of schistosome infection, the participants are referred to the local health system. At the 24 months’ time point, TBST is being applied in both arms.

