### Sample size and statistical analysis

The sample size was calculated in relation to the primary child outcome proportion showing stunted growth at 2 years of age, for which a larger sample size is assumed to be necessary than for the maternal outcome (Hb, 2 years after delivery).

The prevalence of stunting in Madagascar is estimated to be 40% of children under 2 years of age [26]. For our sample size estimate, it was conservatively assumed that:
Twenty per cent of all children at the age of 2 years are stunted (height-for-age *z*-score < − 2)The intervention can reduce the proportion of stunted children by 50% in infected individuals, i.e. to observe that 10% of all children at the age of 2 years are stunted in the intervention arm.

In order to estimate the appropriate number of infected individuals at 9 months of age, sample sizes with power values of 80% and 90% were subsequently calculated using the OpenEpi tool [27]. For a power of 80%, at least 394 infected individuals at 9 months of age would be required and for a power of 90% 526 individuals. The design effect was assumed to be 1.9 by which the initial sample size needs to be multiplied to account for the clustered design of the study. This leads to a sample size of 749 for 80% power and 1000 for 90% power.

With an annual loss to follow-up of 10% from a visit to visit and an infant mortality rate of 4%, 86% of all mother-infant tandems are expected to present for the 9-month visit. For the 2 years visit, a loss to follow-up of around 10% between 9 months and 2 years is assumed, so that around 0.86 × 0.9 = 77.4% of all mother-infant tandems are expected to present for the 2-year visit. To correct for loss to follow-up, we use the factor 1/0.774 = 1.3. Since our analyses only focus on women infected with schistosomiasis, the number of women to be recruited needs adjusting, considering that the expected prevalence of 0.25 results in an additional inflation factor of 4 leading to an inflation factor of 1.3 × 4 = 5.2.

We hence planned to enrol 4200 eligible pregnant women in the 40 randomized cluster of the trial ensuring a power between 80 and 90% and an additional 1000 participants for the cross-sectional sub-study in the non-randomized sites. Based on the 40 randomized clusters identified for this study, an average of 105 women per cluster is needed to be recruited per cluster.

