### Analysis for the primary outcomes

For the main child endpoint, the proportion of stunted children (height-for-age *z*-value < − 2) at 2 years will be compared between the intervention and control arm using the chi-square tests and *t*-tests. Reference standards from Madagascar as reported by the WHO [28] will be considered in the analysis. For the maternal main endpoint, the difference in Hb 2 years after delivery will be compared between the intervention and control arms using the *t*-tests. For all analyses, a significance level of alpha *=* 0.05 is assumed. Additional analyses will be performed using mixed-effects logistic and linear regression models to account for the between-cluster variation as a random effect. Secondary and other outcomes that are normally distributed will be analysed in the same way.

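### The child sample size counts infants infected at 9 months but is converted to recruits with a prevalence applied to women, so the stated 80–90% power is unsupported

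*Protocol article*

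**What the plan says.** All of the sizing is in the protocol article under Sample size and statistical analysis, and it concerns the child endpoint (height-for-age z below −2 at 2 years).

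- Control risk: "Twenty per cent of all children at the age of 2 years are stunted". The section calls this conservative against a cited 40% in under-twos.
- Effect: "The intervention can reduce the proportion of stunted children by 50% in infected individuals". The same sentence then equates this with 10% of all children being stunted in the intervention arm.
- Number required: "at least 394 infected individuals at 9 months of age would be required" for 80% power and 526 for 90%; with the design effect of 1.9, 749 and 1000.
- Conversion to recruits: a factor of 1.3 for retention of 77.4%, and then a further factor, introduced by "Since our analyses only focus on women infected with schistosomiasis" and continued with "considering that the expected prevalence of 0.25 results in an additional inflation factor of 4". The result is 4200 women in 40 clusters, with power said to lie between 80 and 90%.

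Analysis for the primary outcomes compares the proportion stunted between the two arms and names no infection subgroup.

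**The concern.** One calculation uses two populations. The number required is a count of infants with an infection at 9 months. The factor that turns it into a recruitment target is a prevalence applied to pregnant women. An infected mother does not imply an infected 9-month-old. The article gives no infant prevalence and does not say that children of infected women are taken as infected. The analysis section uses a third population, all children.

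What is at stake is the power claimed for a primary endpoint. If infants are infected less often than their mothers, fewer informative children are available than the calculation assumes. If the mother's infection was meant, the effect size was assumed for a different group from the one counted.

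**Working it through.** **Inputs from the article.** Stunting 20% v 10%; "For all analyses, a significance level of alpha *=* 0.05 is assumed" (two-sided is my assumption, as sidedness is not stated); power 80% and 90%; design effect 1.9; retention 0.774; prevalence 0.25; 4200 women; 40 clusters, 1:1.

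**Reproducing the plan's figures.** Unpooled normal approximation, n per arm = (1.96 + z_power)² × (0.2×0.8 + 0.1×0.9) / 0.1²:

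- 80%: 196.2, rounded up to 197; 2 × 197 = 394. 90%: 262.7, rounded up to 263; 2 × 263 = 526. Both match.
- × 1.9: 748.6 and 999.4, given as 749 and 1000.
- × 1.3 × 4 = 5.2: 3895 and 5200 women. 4200 lies between them.

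So the chain was used as written, with the factor of 4 applied to the infant count.

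**Reading A: the set is infants infected at 9 months.** Pairs expected at 2 years: 4200 × 0.774 = 3251.

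- Infant prevalence needed for 80% power: 749 / 3251 = 23.0%.
- For 90% power: 1000 / 3251 = 30.8%.

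Power at other prevalences q: infected children N = 3251 × q; effective n per arm = N / (2 × design effect); power = Φ(0.1 / √(0.25 / n) − 1.96) for 20% v 10%. The prevalences are assumed, because the article gives none.

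The constant-ICC column takes 1.9 to belong to the planned 25%: 3251 × 0.25 / 40 = 20.3 children per cluster, so ICC = 0.9 / 19.3 = 0.047. The design effect is then 1 + (N/40 − 1) × 0.047, which gives 1.52, 1.33 and 1.14 at 15, 10 and 5%. The last column uses 40% v 20%, the same halving from the cited stunting level; there 0.1 becomes 0.2 and 0.25 becomes 0.4×0.6 + 0.2×0.8 = 0.40.

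| Infant prevalence (assumed) | Infected at 2 years | 20% v 10%, design effect 1.9 | 20% v 10%, constant ICC | 40% v 20%, design effect 1.9 |
|---|---|---|---|---|
| 25% | 813 | 83% | 83% | over 99% |
| 15% | 488 | 62% | 72% | 95% |
| 10% | 325 | 46% | 60% | 83% |
| 5% | 163 | 26% | 39% | 54% |

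Example, 15% with design effect 1.9: n = 488 / 3.8 = 128; 0.1 / √(0.25/128) = 2.26; Φ(2.26 − 1.96) = 0.62.

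**Reading B: the set is children of infected women.** The 0.25 is then the right multiplier and about 813 children are available. But 394 and 526 are no longer infants infected at 9 months, and a halving assumed for infected individuals has no stated basis for those children of infected mothers who are not themselves infected. Infant prevalence then enters through the effect size instead of the head count.

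**Against the analysis section.** The comparison by arm described there uses all of the roughly 3251 children and matches neither reading.

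**The case against.** The best defence is that no step is miscalculated and that Reading B makes the factor of 4 legitimate, leaving only a wrong label on 394 and 526. The first half stands: this is an inconsistent definition, not an arithmetic slip, and the 23% threshold belongs to Reading A and to 80% power only. The second half does not rescue the power, because the effect size was assumed in infected individuals.

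A second defence is that 20% control stunting is cautious against the cited 40%. This also stands in part. At 40% v 20%, power stays above 80% down to about 10% infant prevalence, but not at 5%. A fixed design effect of 1.9 also overstates the loss as infected children per cluster become fewer, so the constant-ICC column is the more coherent one.

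A reader might infer more than the article supports:

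- **That the analysis set is chosen by the child's 9-month result, so the randomised comparison is lost.** Since "the POC-CCA-TBST is being implemented among pregnant women between week 20 of pregnancy and delivery", that result does arise after the intervention has begun, and selecting on it would be hazardous. But nothing says that it selects the set, and the primary analysis as described has no such restriction.
- **That infection is measured differently in the two arms.** The Table 5 legend plans laboratory POC-CCA on women's T0 samples, and on women's and children's T3 samples, in all sites. The extra on-site test in the intervention arm matters only if it defines a set, and nothing says that it does.
- **A specific power for Reading B.** This would need the share of infected mothers' children who are infected, and the benefit to the others of treating the mother. The article gives neither.

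**Conclusion.** The concern holds as a contradiction within the sample size section, and between it and the primary analysis. The claimed 80–90% power is not supported for any one population. Under Reading A it needs between 23% and 31% of infants infected at 9 months, a figure that is nowhere stated. Below that, power falls to 62–72% at 15%, 46–60% at 10% and 26–39% at 5% for 20% v 10% stunting, each range running from a fixed design effect to a constant ICC. Control stunting nearer 40% with the same relative effect would offset much of this. Under Reading B the head count is sound and the effect size is unsupported.

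This rests on two-sided 5% testing, the plan's own retention and design effect, and infant prevalences that are assumed. It does not show that the trial is underpowered, since the true infant prevalence is unknown.

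**What to change.** 1. Name one population in the sample size section and use it for the number required, the effect size and the prevalence factor. Align it with Analysis for the primary outcomes.
2. Keep the unrestricted comparison by arm as primary. Making children of infected mothers the primary set would change the estimand during follow-up, drop about three quarters of the children, and leave out infected infants of uninfected mothers.
3. Define any infection subgroup by the mother's T0 laboratory POC-CCA result: the urine is taken at enrolment, before treatment, and the assay is the same in both arms. Treat a subgroup defined by the child's 9-month result as exploratory.
4. Restate the power for the chosen population as a function of infant prevalence and control stunting, using the pooled, arm-blind T3 laboratory prevalence once available.

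The cost is wording and a blinded count from tests already planned. Recruitment closed in February 2020, so the sample size itself cannot change. The downside is that the restated power may be less favourable. As an illustration for the unrestricted comparison: if 25% of infants were infected, stunting halved only in them, and the rest stayed at 20%, the contrast would be 20% v 17.5% (0.20 − 0.25 × 0.10), with power about 26% at a design effect of 1.9. If instead the halving applied to all children, as the section's 10% figure reads literally, power would exceed 99%. That spread is why the population and effect need to be stated together.

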### Analysis for the primary outcomes

For the main child endpoint, the proportion of stunted children (height-for-age *z*-value < − 2) at 2 years will be compared between the intervention and control arm using the chi-square tests and *t*-tests. Reference standards from Madagascar as reported by the WHO [28] will be considered in the analysis. For the maternal main endpoint, the difference in Hb 2 years after delivery will be compared between the intervention and control arms using the *t*-tests. For all analyses, a significance level of alpha *=* 0.05 is assumed. Additional analyses will be performed using mixed-effects logistic and linear regression models to account for the between-cluster variation as a random effect. Secondary and other outcomes that are normally distributed will be analysed in the same way.

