**Table 3 Tab3:**
[figure not shown]
Scheme of scheduled visits. T0 mothers enrolment at 5^th^ or 6^th^ month of pregnancy pregnancy; T1 pre-delivery follow up at the 8^th^ month of pregnancy; T2 delivery follow up at birth and inclusion of children; T3 follow up 9 month after delivery; and, T4 final follow up 24 months after delivery

T0: mother’s enrolment during the 5th or 6th month of pregnancy. Haemoglobin is measured on-site using the Hemocue® system, and a urine sample is being collected (≥ 25 ml). In the TBST intervention arm, the POC-CCA to test for schistosomiasis infection is done on-site. Women who test positive are offered (40 mg/kg) PZQ treatment. Additional samples (Table 4) are being collected at the non-randomized sites for the cross-sectional sub-study to assess the sensitivity and specificity of the POC-CCA test against a panel of reference tests described in Table 4.T1: 1st follow-up, 8th month of pregnancy. Haemoglobin is measured on-site by means of the Hemocue® system.T2: 2nd follow-up, delivery and child enrolment. The case report form (CRF) is completed. The newborns are included, unless the mother decides to withdraw her/him from the study. Weight and height of the newborns are measured.T3: 3rd follow-up, 9 months after delivery/birth. Haemoglobin is measured for all women using the Hemocue® system. Height and weight are measured for all children. A urine sample is being collected (≥ 25 ml) from all mothers and children. In the TBST intervention arm, the POC-CCA to test for schistosomiasis infection is being performed on-site for the mother and child. To test-positive mothers, a 40 mg/kg dose of PZQ treatment is offered. Test-positive children are treated with 300 mg.T4: 4th follow-up, 24 months after delivery/birth. Haemoglobin is measured for all mothers on-site using the Hemocue® system. Height and weight are measured for all children. A urine sample is being collected (≥ 25 ml) from all the women and children. In both arms, the POC-CCA test for schistosomiasis infection is being performed on-site for the mothers and children. All positive women and children are offered 40 mg/kg and 300 mg PZQ treatment, respectively.

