**Table 4 Tab4:**
[figure not shown]
Scheme of scheduled visits. At T0 blood and stool samples will be collected from 1000 women, urine samples from 5200 women. At T1 capillary blood will be collected from 5200 women. At T2 no biological samples will be collected. At T3 and T4 capillary blood will be collected from all the women attending the follow-up visit, urine will be collected from all the participants attending the follow-up visit. Considering the loss to follow up 4472 mothers and 4472 children are expected at T3 to remain in the study and 3900 women and 3900 children at 4. UCP-CF (Up-Converting Phosphor – Consecutive Flow) antibody assay will be performed on serum samples. Hb will be measured on capillary blood. UCP-LF-CAA (Up-Converting Phosphor – Lateral Flow) and POC-CCA will be performed on urine samples. PCR will be performed on urine, plasma and stool samples. Microscopy will be performed on stool samples

All the samples collected for further laboratory analysis at the two non-randomized centres are stored on-site at the required temperatures and delivered to the laboratories within 1 week. Tables 4 and 5 summarize the testing and the sampling schemes. The tests will be performed according to standardized protocols described in [11–15, 18–25].

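### The named primary tests use only the 24-month value, although about a fifth to a quarter of tandems are expected to be absent then, and give no role to the haemoglobin and child size recorded earlier

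*Protocol article*

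**What the plan says.** All references are to the protocol article.

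- **Analysis for the primary outcomes.** The proportion stunted "at 2 years will be compared between the intervention and control arm using the chi-square tests and" t-tests. Hb 2 years after delivery is compared between arms by t-tests. Mixed-effects logistic and linear models are listed as additional analyses, described only as handling between-cluster variation. No earlier measurement is named in any of these analyses.
- **Sample size and statistical analysis.** The attendance foreseen at 9 months is given as "With an annual loss to follow-up of 10% from a visit to visit and an infant mortality rate of 4%, 86% of all mother-infant tandems"; for 24 months the figure is "around 0.86 × 0.9 = 77.4% of all mother-infant tandems are expected to present for the 2-year visit". The response is to enrol more: "To correct for loss to follow-up, we use the factor 1/0.774 = 1.3".
- **Table 4 legend.** "4472 mothers and 4472 children are expected at T3 to remain in the study and 3900 women and 3900 children at 4" (the last figure refers to T4), out of 5200 enrolled.
- **Data collection plan.** At T3: "Haemoglobin is measured for all women using the Hemocue® system. Height and weight are measured for all children". Newborn weight and height are taken at T2, and maternal Hb also at T0 and T1.
- **Intervention.** "In the study centres of the control arm, no TBST is carried out" until the 24-month visit, when both arms receive it.

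**The concern.** Both primary endpoints exist only for those seen at T4. Raising enrolment by 1.3 restores the expected number of observations, but it does not make those seen in one arm comparable with those seen in the other. An unadjusted test of the observed 24-month values is unbiased only if loss is unrelated to the outcome, or related to it in the same way and to the same extent in both arms.

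The trial also collects, at scheduled visits, measurements that should predict the missing values and explain part of the variation in the observed ones. A pre-treatment Hb (T0) is available for women, with further values at T1 and T3. Children have size at birth and at 9 months. The tests as named set all of this aside. At stake are precision that costs nothing to recover, and some protection against loss that depends on how a child was growing or how anaemic a mother was.

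**Working it through.** **1. The plan's retention figure reproduces.** Inputs from Sample size and statistical analysis: 10% loss and 4% infant mortality to 9 months, then 10% loss to 24 months.
- Present at T3: 1 − 0.10 − 0.04 = 0.86
- Present at T4: 0.86 × 0.9 = 0.774, so 22.6% are absent
- Of 4200 in the randomized clusters: 4200 × 0.774 = 3251 present, 949 absent

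**2. Who the absent are.**
- Already absent at T3: 0.14 × 4200 = 588, including about 0.04 × 4200 = 168 infant deaths
- Seen at T3 but not T4: 0.86 × 0.1 = 8.6%, or 361 tandems; 8.6 / 22.6 = 38% of the absent
- Mothers, setting infant death aside: 1 − 0.9 × 0.9 = 19%
- Table 4 legend: 4472 / 5200 = 86% at T3, as above, but 3900 / 5200 = 75% at T4, so 25% absent. The text's 77.4% would give 5200 × 0.774 = 4025.

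**3. Size of a possible bias in stunting.** The documents give no dropout mechanism, so everything in this step is assumed except the 20% stunting rate and the average loss. True stunting is 20% in both arms, so any difference is bias.

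*Scenario A: loss between T3 and T4 depends on 9-month height-for-age z.* Let z at 9 and 24 months be bivariate normal with correlation r, and let the log-odds of staying be a + b·z(9 months), with a set so that average retention is 0.9. Loss before T3 is random. The proportion stunted among those seen is E[retention × P(stunted | z at 9 months)] / 0.9. The shortfall below 20%, in percentage points, is:

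| r | b = 0 | b = 0.5 | b = 0.75 | b = 1.0 |
|---|---|---|---|---|
| 0.5 | 0 | 0.74 | 1.11 | 1.45 |
| 0.7 | 0 | 1.06 | 1.61 | 2.13 |
| 0.8 | 0 | 1.23 | 1.88 | 2.49 |

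- Same b in both arms: bias 0.
- Dependence in one arm only, b = 0.5 to 1.0: bias 0.7 to 2.5 points.
- b = 0.5 in one arm and 0.75 in the other: 1.11 − 0.74 = 0.4 points (r = 0.5) to 1.88 − 1.23 = 0.65 points (r = 0.8).

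*Scenario B: amount of loss differs by arm.* Loss averages 22.6%, and absent children are RR times as likely to be stunted as those seen. The observed proportion at loss m is 0.20 / (1 − m + m·RR). The bias is the difference between arms:

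| Loss by arm | RR = 1 | RR = 1.5 | RR = 2 |
|---|---|---|---|
| 22.6% v 22.6% | 0 | 0 | 0 |
| 19.6% v 25.6% | 0 | 0.5 | 0.8 |
| 17.6% v 27.6% | 0 | 0.8 | 1.3 |
| 12.6% v 32.6% | 0 | 1.6 | 2.7 |

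**4. Against the standard error.**
- All tandems seen, 3251 / 2 = 1625 per arm: √(2 × 0.2 × 0.8 / 1625) = 1.40 points; × √1.9 (the plan's design effect) = 1.93. A bias of 2.5 points is 1.3 standard errors.
- If only infected participants are analysed, at the plan's prevalence of 0.25 (406 per arm): √(2 × 0.2 × 0.8 / 406) = 2.81 points; × √1.9 = 3.87. The same bias is then about 0.64 standard errors.

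**5. What the earlier data can recover.** Under Scenario A, simulated regression imputation of 24-month z from 9-month z left at most 0.15 points of bias. That is a best case: loss before T3 is random, and the imputation model matches the one that generated the data.

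**6. Precision.** Adjusting for a baseline value with correlation ρ to the outcome multiplies the individual-level residual variance by about 1 − ρ². The documents give no ρ for Hb, so the gain is not sized here.

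**The case against.** - **The article never says that only attenders are analysed.** This stands. Naming a chi-square test or t-test does not rule out imputing first. The analysis set and missing-data rules are commonly left to the full protocol or SAP, which are not shown, so their absence is no finding. The point here concerns the method that is stated.
- **Nothing in the documents predicts unequal loss.** This stands. The visit schedule is the same in both arms, testing and treatment are offered to everyone at 24 months, and Community engagement and social mobilization describes reminders and other retention work. On the other side, the Randomization section says blinding at centre level is not possible, and before 24 months only intervention families are tested and offered treatment. That makes unequal loss possible, not expected. A reader might infer that arm-dependent loss will bias the result; the documents do not support that.
- **The larger bias figures come from one-sided scenarios.** This stands. The upper end needs growth-related loss in one arm only, or a very uneven split of losses. The range must start at 0.
- **The 22.6% is not all missing data and does not apply unchanged to mothers.** This stands. A child who died has no 24-month height to impute, and infant death does not remove the mother's Hb.
- **Mixed models are already planned.** Only in part: they are additional rather than primary, and are described as handling clustering, with no earlier visit named.
- **The planned difference is 10 points, so the bias is small.** That difference is assumed in infected individuals. The primary analysis text does not restrict the comparison to them. If all children are compared, the implied difference is about 0.25 × 10 = 2.5 points, similar to the top of the bias range.

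**Conclusion.** The point holds as a weakness in the stated primary method, not as a demonstrated bias. Unadjusted tests on the single 24-month value are named as the primary comparisons, while the plan expects 22.6% of tandems to be absent (about 4 points of it infant death; about 19% for mothers; 25% by the Table 4 legend). Hb and child size already scheduled at earlier visits go unused in those tests.

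Precision is lost to the extent that earlier values predict later ones. Bias arises only if loss depends on earlier growth or Hb differently by arm. For stunting it runs from 0 to about 2.5 points in the assumed dropout models, and reaches 2.7 only with the most uneven loss split tried. These figures rest on assumed slopes, correlations and risk ratios that are not in the documents. Whatever an unseen SAP says about missing data, a model using the earlier measurements improves on the tests named here.

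**What to change.** In Analysis for the primary outcomes:

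1. **Mother.** Make the primary analysis a likelihood-based linear mixed model of Hb at T1, T3 and T4, with T0 Hb and region as covariates and health centre (CSB) and woman as random effects. Report the arm contrast at T4.
2. **Child.** Analyse 24-month stunting with CSB as a random effect and region as a covariate. Add an analysis that multiply imputes 24-month height-for-age z, by arm, from T2 and T3 size, and derives stunting from the imputed z. Do not impute for children who died.
3. **Sensitivity and reporting.** Keep the unadjusted comparison of observed 24-month values as a sensitivity analysis. Report attendance by arm at T3 and T4, with deaths shown separately.
4. **Consistency.** Reconcile the 77.4% in the sample size text with the 75% implied by the Table 4 legend.

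If the SAP already does this, only the article's wording needs aligning. The cost is modest analysis work, with no new visits or data. The results would rest on data being missing at random given the earlier measurements. The correction is partial: 9-month data exist for only about 38% of absent tandems, and the rest depend on birth size or on T0 and T1 Hb.

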### Randomization

Randomization was done at the CSB level. For randomization, a list with the codes of the 20 CSBs in the regions of Bongolava and Itasy (so-called Antananarivo sites) and 20 CSBs in the region of Amoron’i Mania (so-called Fianarantsoa sites) was provided to the Leiden University Medical Center (LUMC), which randomly allocated 10 of the sites to control and 10 to intervention arm stratified by regions. LUMC informed the University of Antananarivo, University of Fianarantsoa and BNITM about the randomization result.

While blinding at the CSB level is not possible, all procedures of the study and of TBST (including urine sampling) are implemented at both the intervention and control CSBs. Only the actual POC-CCA test and the treatment of positives are exclusively done in intervention sites. In the participant ID, an alphanumeric element will define the recruitment site of the women. In case women would change the study site during the course of the study, the study nurses would be able to identify the non-correspondence of the site from the participant ID. This ensures that the randomization scheme is kept.

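### Both primary endpoints are tested with chi-square and t-tests that ignore the 40 randomised health centres, and the models that allow for clustering are only additional

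*Protocol article*

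**What the plan says.** Under Randomization, the protocol article states: "Randomization was done at the CSB level". In each of the two study areas, 20 CSBs were on the list, and the allocating centre "randomly allocated 10 of the sites to control and 10 to intervention arm stratified by regions". That makes 40 clusters, 20 per arm.

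Under Sample size and statistical analysis, clustering is recognised: "The design effect was assumed to be 1.9 by which the initial sample size needs to be multiplied". The same section says that the analyses concern infected women only, and it divides by an expected prevalence of 0.25 to reach the enrolment target.

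Under Analysis for the primary outcomes, the proportion of stunted children "at 2 years will be compared between the intervention and control arm using the chi-square tests and" t-tests. Maternal Hb is also compared by an unadjusted t-test. The error level is common to every comparison: "a significance level of alpha *=* 0.05 is assumed". Clustering comes in only afterwards: "Additional analyses will be performed using mixed-effects logistic and linear regression models to account for the between-cluster variation as a random effect". Neither this section nor Outcomes restricts the child endpoint to infected children or to children of infected mothers.

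**The concern.** Children and mothers seen at the same CSB share a catchment area, its exposure to infection, its food supply and its staff, so their outcomes are likely to be correlated. A chi-square or t-test on individuals treats them as independent and understates the standard error of the difference between arms. The protocol expects such correlation, since it nearly doubles the sample size because of it, and then leaves it out of the tests named for the primary comparison.

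What is at stake is a false claim of benefit. If an unadjusted test gives p < 0.05 and the mixed model does not, the plan as written points to the unadjusted result. The Discussion says that positive findings would be used to promote the strategy in national guidelines. The analysis section also extends the same approach to normally distributed secondary and other outcomes.

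A smaller point in the same sentence is that two kinds of test are named for one binary endpoint, without saying which decides.

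**Working it through.** **Inputs from the protocol article.** 40 clusters; 20% against 10% stunted; alpha 0.05; design effect (DE) 1.9; 4200 women enrolled in the randomised clusters; 77.4% of pairs retained to 2 years; infection prevalence 0.25. Sidedness is not stated, but a two-sided test reproduces the plan's figures. No ICC is given.

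**Step 1: reproduce the plan's sample size.** With the unpooled two-proportion formula, n per arm = (z for alpha + z for power)² × (0.2×0.8 + 0.1×0.9) / 0.1².
- 80% power: 196.2, so 197 per arm and 394 in total. 394 × 1.9 = 748.6, stated as 749.
- 90% power: 262.7, so 263 per arm and 526 in total. 526 × 1.9 = 999.4, stated as 1000.

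All four figures agree with the article, so the design effect of 1.9 is a working part of the plan.

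**Step 2: true size of an unadjusted test at that design effect.** If the true variance is DE times the variance that the test assumes, then

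size = 2 × [1 − Φ(1.96 / √DE)].

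With DE = 1.9, √1.9 = 1.38 and 1.96 / 1.38 = 1.42, so the size is 15.5%.

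**Step 3: cluster sizes at 2 years.** 4200 × 0.774 = 3251 children, and 3251 / 40 = 81.3 per cluster. A quarter of these gives 20.3 infected pairs per cluster.

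**Step 4: dependence on what 1.9 refers to.** With DE = 1 + (m − 1) × ICC, the implied ICC is 0.9 / (m₀ − 1), where m₀ is the cluster size for which 1.9 was meant. The design effect that matters is then 1 + (m − 1) × ICC at the cluster size m that is analysed.

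| 1.9 set for (m₀) | Analysed (m) | Implied ICC | DE at analysis | True size |
|---|---|---|---|---|
| infected pairs, 20.3 | infected pairs, 20.3 | 0.047 | 1.90 | 15.5% |
| all children, 81.3 | all children, 81.3 | 0.011 | 1.90 | 15.5% |
| all children, 81.3 | infected pairs, 20.3 | 0.011 | 1.22 | 7.6% |
| 1000/40 = 25 infected | all children, 81.3 | 0.0375 | 4.01 | 32.8% |
| infected pairs, 20.3 | all children, 81.3 | 0.047 | 4.74 | 36.8% |
| 749/40 = 18.7 infected | all children, 81.3 | 0.051 | 5.08 | 38.4% |

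The table uses cluster sizes at analysis. Tying 1.9 to the 105 women enrolled per cluster would give 7.0% for infected pairs and 13.2% for all children.

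**Step 5: simulation check.** I simulated beta-binomial data with no treatment effect, 20 equal clusters per arm, 20% stunted and 20,000 replicates. The unadjusted test rejected in about 16% (20 per cluster, ICC 0.047) and 15% (81 per cluster, ICC 0.011) of replicates. It rejected in about 37% with 81 per cluster and ICC 0.047. A t-test on the cluster proportions stayed close to 5% in each case. Unequal cluster sizes, which would tend to raise the error, and the regional strata, which could lower it, were left out.

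**Step 6: maternal Hb.** The sample size rests on stunting alone, and no standard deviation, ICC or design effect is given for Hb. The formula in Step 2 then shows only the direction: any ICC above zero makes DE exceed 1 and the size exceed 5%.

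**The case against.** The strongest reply is that mixed models are already planned, so a cluster-aware result will be available for both endpoints. That is true, and it makes the problem cheap to cure. It does not remove the problem, because the models are presented as additional to the tests named for the primary comparison. Nor is this detail left to an analysis plan that is not shown: the article names the tests and their order.

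One might also say that the t-tests are meant for cluster-level proportions, a recognised method that would explain a t-test beside a binary endpoint. Nothing says so. The Trial design section names children and mothers as the units of analysis, a standard chi-square test works on individuals, and the task of handling between-cluster variation is given to the additional models.

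Objections to the size carry more weight. The 1.9 is a planning assumption, not an estimate. A reader might infer that the real error rate is 16% to 37% for both endpoints, or that standard errors are too small by at least √1.9. The documents support neither. The 37% needs 1.9 to belong to about 20 infected pairs per cluster while all of about 81 children are analysed. The conflict in the text makes that possible, but it does not establish it. The opposite mismatch gives a standard error ratio of only √1.22 = 1.10 and an error of 7.6%, so 15.5% is not a floor. For Hb no figure can be derived at all.

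**Conclusion.** The point holds. The tests named for both primary endpoints leave out the unit of randomisation, against the protocol's own allowance for clustering, and nothing else in the article corrects this.

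For stunting, the best-supported figure is about 15.5% in place of 5%. It assumes a two-sided test and a design effect of 1.9 in the set that is analysed. Across the readings in the table the figure lies between about 8% and 38%, and every one of them exceeds 5%. The width of that range comes from the missing ICC and from the conflict over infected pairs or all children, not from the choice of test itself. For Hb the conclusion is qualitative: the error is inflated if there is any positive correlation within CSBs, by an amount that the article does not allow one to calculate.

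Confidence is high in the defect and moderate in the figures. It should be corrected before the data are analysed, because it decides whether a positive primary result can be believed.

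**What to change.** In Analysis for the primary outcomes, make a cluster-aware analysis primary for each endpoint: the logistic mixed model for stunting and the linear mixed model for Hb that are already planned. Each needs a CSB random effect, the region stratum used in the randomisation and a small-sample correction for 40 clusters. An equivalent cluster-level analysis would serve as well. Name that analysis as the single deciding test for its endpoint. Keep the unadjusted chi-square and t-tests as descriptive only, or delete them. The choice of effect measure and the exact degrees of freedom can be left to the statistical analysis plan.

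The same revision should say whether infected pairs or all children form the primary analysis set, and to which cluster size the 1.9 refers.

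The cost is a change of wording before database lock. Standard errors become larger but correct, and no extra data are needed.
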